#### 4.4. Sample size

A sample size of 1760 adolescents calculated using a Cluster Randomized Controlled Trial formula (RCT) and adjustment to account for design effect and 10% loss to follow up as shown below is expected to be sufficient for the study.

- (i) Sample size formula for RCT considering simple random sampling:

$$2N = \frac{4(Z_{\alpha} + Z_{\beta})^2 \sigma^2}{\delta^2}$$

Where

2N is number of participants in two arms

$Z_{\alpha}$  is point on standard normal distribution corresponding to level of confidence of the study estimated to be 1.96 for 95% Confidence Interval

$Z_{\beta}$  is value corresponding to 85% power of the study =1.03

$\sigma$  is known mean DMFT from a previous study in Ndola, Zambia by Nasilele et al (2018)=1.34

$\delta$  is the expected clinically significant change in mean DMFT set at 20% =0.268

Based on assumptions and known values above the sample size for 2 arms is calculated as follow:

$$2N = \frac{4(1.96+1.03)^2 (1.34)^2}{(0.268)^2}$$

$$2N = 894.01 = 894$$

- (ii) Sample size considering cluster design, hence adjusting for design effect

$$n_c = n_1 [1 + (m - 1) \rho]$$

$$n_c = 894 [1 + (80 - 1) 0.01]$$

$$n_c = \text{estimated to be } 1600.26 = 1600$$

Where

$n_c$  = Number of pupils/participants in cluster per arm

$n_1$  = Individual number of participants (pupils) in an arm when considering random sampling

$\rho$  = Estimated intra-cluster correlation coefficient (ICC) to be 0.01

$m$  = Estimated cluster size in this study is 80 students in a class

- (iii) Sample size adjustment to consider loss to follow up assumed at 10%

$$n_c = 1600 + \{1600 \times (10/100)\} = 1760$$

$$\text{Final minimum sample size considered} = 1760$$

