#### **4.10. Study outcomes**

The expected primary outcomes are improved oral health (dental caries status and gingivitis) and OHRQoL. The secondary outcomes include improved oral hygiene (plaque score) and oral health knowledge and related behaviors. The effect sizes for improvement in oral health and oral health related quality of life are based on average improvement achieved in similar studies reviewed.

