#### **4.12. Data entry cleaning and analysis**

Data entry, coding and processing will be done using a computer software program IBM SPSS for Windows (Version 23). Frequency distribution for proportions, means (SD), cross tabulation with chi –square and binary logistic regression reported in odds ratio and 95% (CI) will be performed per respective objectives.

Frequency distribution for proportions of adolescents with plaque, gingival bleeding, poor oral health behaviors and oral health related quality of life. Dental caries experience will be summarized as number and percentage. Furthermore, cross tabulation for bivariate comparison of differences in intervention outcome variables by socio-demographics, study arms and oral health behaviors will be conducted. To examine for the differences between the groups (effectiveness of trial intervention) generalized estimating equations will be performed and reported in odds ratio and 95% confidence interval. A statistical significance difference shall be assumed when  $p \leq 0.05$ . Analysis plan per objective is summarized in appendix 6.

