## Appendix 6- Analysis Plan by objectives

| No | Objective                                                                                                                                                                       | Analysis                                                                   | To be reported as                                              |
|----|---------------------------------------------------------------------------------------------------------------------------------------------------------------------------------|----------------------------------------------------------------------------|----------------------------------------------------------------|
| 1  | To determine prevalence and distribution of dental caries, periodontal conditions and oral impacts on daily performance among adolescents in Copperbelt Province, Zambia        | Frequency distribution, chi-square test, logistic regression               | Number and percentage, odds ratio with 95% confidence interval |
| 2  | To determine the association between dental caries and oral health related quality of life among adolescents in Copperbelt Province                                             | Frequency distribution, chi-square test, hierarchical logistic regression  | Number and percentage, odds ratio with 95% confidence interval |
| 3  | To assess the effects of a six months modified basic package of oral care intervention on knowledge and behaviors related to dental caries after 18 and 24 months of follow up. | Frequency distribution, chi-square test, generalized estimating estimation | Number and percentage, odds ratio with 95% confidence interval |
| 4  | To assess the effects of a six months modified basic package of oral care intervention on prevalence of dental caries after 6 and 12 months of follow up                        | Frequency distribution, chi-square test, generalized estimating estimation | Number and percentage, odds ratio with 95% confidence interval |
| 5  | To assess the effects of a six months modified basic package of oral care intervention on prevalence of oral impacts on daily performance after 18 and 24 months of follow up   | Frequency distribution, chi-square test, generalized estimating estimation | Number and percentage, odds ratio with 95% confidence interval |

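### The 85% power in section 4.4 is for a difference in mean DMFT, which no planned test uses, and it is not established even for DMFT; power for the prevalence tests is left undetermined

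*Protocol*

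**What the plan says.** **Sample size (Protocol, 4.4).** A two-means formula is used, with 1.96 for a two-sided 5% test and 1.03 for 85% power. The number entered as sigma, 1.34, "is known mean DMFT from a previous study in Ndola, Zambia". The difference to be detected is defined from that same number: it "is the expected clinically significant change in mean DMFT set at 20% =0.268". The result, 894, is multiplied by a design effect with cluster size 80 and "Estimated intra-cluster correlation coefficient (ICC) to be 0.01", then raised by 10% for loss to follow-up. The total of 1,760 is presented as enough for the whole study.

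**Outcomes (4.10).** The primary outcomes are caries status, gingivitis and OHRQoL. The effect sizes for oral health and OHRQoL "are based on average improvement achieved in similar studies reviewed". No figure follows.

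**Objectives and measures.** Objectives 4 and 5 (2.2) concern the prevalence of caries and of oral impacts. Caries is recorded with CAST codes.

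**Analysis.** Section 4.12 states: "Dental caries experience will be summarized as number and percentage". Effectiveness is tested by generalized estimating equations with odds ratios. All five rows of Appendix 6 report "Number and percentage, odds ratio with 95% confidence interval".

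Outside 4.4, DMFT appears only in the abbreviation list and in one background figure in 1.1.

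**The concern.** The protocol's only power statement concerns a quantity that is never compared between arms. For a difference in means, power depends on the ratio of the difference to the SD. For a prevalence contrast it depends on the control prevalence and the size of the reduction, and the protocol fixes neither. The 85% cannot be carried from one to the other.

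Sections 4.4 and 4.10 also conflict. One sets a 20% DMFT change as clinically significant; the other says the effect sizes are averages from reviewed studies, but no such average is stated anywhere.

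At stake is how the results are read. A non-significant odds ratio for caries or oral impacts would be reported as coming from a test with 85% power, although no such power was worked out for that test. The protocol describes this class of trial as giving a definitive assessment, so that reading would carry weight.

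**Working it through.** **1. The protocol's own figure reproduces.**
- 2N = 4 × (1.96 + 1.03)² × 1.34² / 0.268² = 894.01.
- Design effect = 1 + (80 − 1) × 0.01 = 1.79; 894 × 1.79 = 1,600.26, taken as 1,600.
- 1,600 × 1.1 = 1,760.
- Effective n per arm = 1,600 / 1.79 / 2 = 446.9. Power for the mean comparison = Φ(0.2 × √(446.9/2) − 1.96) = 0.848.

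**2. The DMFT inputs cancel.** Sigma is entered as 1.34, described as a mean, and delta is 20% of the same 1.34. So delta/sigma = 0.2 whatever the data, and 2N = 4 × 2.99² / 0.2² = 894.01 with any value in place of 1.34. No SD of DMFT is given, so the 85% is not established for mean DMFT.

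**3. Power for a prevalence contrast with the same n and design effect.** With control prevalence p and q = p × (1 − relative reduction), two-sided 5%, unpooled normal approximation:

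Power = Φ( (p − q) / √[(p(1 − p) + q(1 − q)) / 446.9] − 1.96 )

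Worked case, p = 0.40, q = 0.32: SE = √[(0.2400 + 0.2176)/446.9] = 0.0320; 0.08/0.0320 = 2.50; Φ(0.54) = 0.71.

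The 20% column is an assumption: it carries the DMFT change over to prevalence, which 4.4 does not do. The 24% and 50% columns are the ends of the range of caries reductions quoted in section 3; 37% is its midpoint. The prevalences 8.8% and 50.98% are the ends of the African caries range in section 3.

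| Control prevalence | 20% | 24% | 37% | 50% |
|---|---|---|---|---|
| 8.8% | 0.16 | 0.22 | 0.47 | 0.76 |
| 20% | 0.34 | 0.47 | 0.85 | 0.99 |
| 30% | 0.53 | 0.69 | 0.97 | >0.99 |
| 40% | 0.71 | 0.86 | >0.99 | >0.99 |
| 50% | 0.86 | 0.95 | >0.99 | >0.99 |
| 50.98% | 0.87 | 0.96 | >0.99 | >0.99 |

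**4. Gingival bleeding.** Section 3 quotes a 10.3–50% reduction in the proportion with bleeding, and an African gingivitis prevalence of 26.7–40.9%. At 10.3%, power is 0.16 to 0.25 over that prevalence range; at 30% (about the midpoint), 0.82 to 0.97; at 50%, above 0.99.

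**5. Oral impacts.** Section 3 quotes a 13.7% improvement without saying whether it is relative or absolute. At 40% control prevalence, power is 0.40 if relative (to 34.5%) and 0.99 if percentage points (to 26.3%). A 20% relative reduction over the Zambian range of 11.7–61.5% gives 0.21 to 0.96.

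**6. Cluster numbers.** Section 4.4 uses clusters of 80. Section 4.5 plans 18 clusters; 4.7 allocates four schools in each of three districts, which is 12. Spreading 1,760 over these numbers, with ICC 0.01, 1,600 analysed and a 20% reduction from 50%:
- 18 clusters: m = 97.8, design effect 1.968, power 0.82.
- 12 clusters: m = 146.7, design effect 2.457, power 0.73.

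**The case against.** **DMFT could be derived from CAST codes, and 4.12 mentions means with SDs.** Both are true. But no between-arm comparison of mean DMFT is planned, and effectiveness is assigned to odds ratios from GEE.

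**The trial may be adequately powered.** A reader might infer from the 20% column that power is well below 85%. The documents do not support that. The 20% was set for mean DMFT, not for a prevalence, and the caries reductions quantified in section 3 are larger (24–50%), although section 3 also notes studies without conclusive evidence. Section 1.2 puts caries and periodontal disease at 40–90% of adolescents in low and middle-income countries, and at 50% or more even a 20% reduction gives about 0.86. Whether the quoted prevalences use this protocol's caries definition, which includes visible enamel change, cannot be told. This part of the objection stands: low power is not shown.

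**Not every primary outcome has a prevalence test in Appendix 6.** This also stands. Gingivitis has no intervention-effect objective and no effect row; its odds-ratio test rests on the Summary and the general wording of 4.12. The mismatch is firmest for caries and oral impacts.

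**The 85% is at least right for mean DMFT.** A reader might infer this because the arithmetic reproduces. It does not follow, since a mean stands where an SD belongs.

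**Conclusion.** The point holds as a mismatch between the stated power and the planned tests. The 85% describes a mean-DMFT comparison that no objective, outcome or analysis row contains, and it is unsupported even there without a true SD. The 4.10 statement about effect sizes has no figure behind it and does not match the 20% in 4.4.

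Power for the prevalence tests is undetermined. For caries, over the African prevalence range and the reductions of 24–50% quoted in section 3, it runs from 0.22 to above 0.99. These figures assume 1,600 analysed, ICC 0.01, cluster size 80 and a single two-group comparison at 5%. The cluster numbers in 4.5 or 4.7 would lower them. The GEE as planned may differ somewhat from this approximation, but the dependence on prevalence and effect size would remain.

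**What to change.** **In 4.4**, replace the single 85% claim with the power of 1,760 for the prevalence of caries, of gingival bleeding and of oral impacts. Show it over the control prevalences in section 3 and the effects reviewed there: caries 24–50%, gingival bleeding 10.3–50%, oral impacts 13.7% (stating whether that is relative or absolute). Use the cluster number and size actually planned, after reconciling 4.4, 4.5 and 4.7. Do not state that 85% holds for mean DMFT unless a true SD is supplied.

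**In 4.10**, give the effect size used for each primary outcome, or delete the statement that effect sizes are averages from reviewed studies.

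**Cost.** This is a change of wording and a short recalculation; no participants need be added. The downside is that the stated power may be less favourable for some outcomes.

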#### **4.5. Sampling**

A two-stage cluster sampling technique will be used; district being a sampling unit at stage one and secondary schools at stage two. Through simple random sampling, three out of ten districts of Copperbelt province will be selected and from each district a total of six clusters (secondary schools) will thereafter be selected as part of the study. To attain a sample size of 1,760 participants, 18 clusters with cluster size of 90-100 will be involved. All adolescents aged 10-14 in grade 8 at selected clusters will be eligible to participate in this study.

#### **4.6. The trial intervention**

The trial intervention is a modified WHO –BPOC which include all the 3 packages of BPOC plus oral health education. The first package, Oral Urgent Treatment (OUT) will include simple extraction of teeth beyond restorable condition and referral for teeth requiring clinic set up for removal. The second package which is Atraumatic Restorative Treatment (ART) will be executed using hand instruments only by removing decayed part of teeth with cavities not reaching the pulp or not diagnosed as irreversible pulpitis then filling with Fuji IX Glass- ionomer. The third component (Affordable Fluoridated Tooth pastes) will be done by providing 250g pack of fluoride toothpaste every two months and toothbrushes every three months for 18 months. In addition to WHO-BPOC the study will also give peer provided oral health education. The peer educators will be furnished with the following printed messages to deliver to their classmates in the intervention groups once after every two weeks for a period of 18 months;

1. Restrict the frequency of taking sugary food and drinks in the diet to less than five times per day.
2. Brush your teeth for 2 minutes ensuring all the surfaces are cleaned; twice per day in the morning and evening before retiring to bed.
3. Use fluoride toothpaste to brush, spit the foam but do not rinse it out.
4. Change your toothbrush every 3 months or when bristles flare out.
5. Advise your parent or guardian to buy a tooth paste containing at least 1450 ppm fluoride and to take you for dental check up at least once a year.

**Table 1 Summary of intervention set up**

| Baseline
data
collection                                                                                                            | Randomization | Activities in each group                       | Activity Schedule                                |                 |                 |                 |                 |                 |                 |                 |                 |         |                  |
|-------------------------------------------------------------------------------------------------------------------------------------------|---------------|------------------------------------------------|--------------------------------------------------|-----------------|-----------------|-----------------|-----------------|-----------------|-----------------|-----------------|-----------------|---------|------------------|
|                                                                                                                                           |               |                                                | Months                                           |                 |                 |                 |                 |                 |                 |                 |                 |         |                  |
|                                                                                                                                           |               |                                                | 1-2                                              | 3-4             | 5-6             | 7-8             | 9-10            | 11-12           | 13-14           | 15-16           | 17-18           | 19-24   |                  |
| 

• OHK

• OHRB

• Plaque

• Gingival bleeding

• Dental caries

 | Intervention  | 1. Peer led OHE                                | OHE once after every 2 weeks (total 36 sessions) |                 |                 |                 |                 |                 |                 |                 |                 | -No OHE |                  |
|                                                                                                                                           |               | 2. OUT sessions 1-3                            | 1 st                                  |                 |                 |                 |                 | 2 nd |                 |                 | 3 rd | No OUT  |                  |
|                                                                                                                                           |               | 3. ART sessions 1-3                            | 1 st                                  |                 |                 |                 |                 | 2 nd |                 |                 | 3 rd | NO ART  |                  |
|                                                                                                                                           |               | 4. AFT sessions 1-9                            | 1 st                                  | 2 nd | 3 rd | 4 th | 5 th | 6 th | 7 th | 8 th | 9 th | -No AFT |                  |
|                                                                                                                                           |               | 5. Follow ups (at 3, 6, 12, 18, and 24 months) |                                                  |                 | 1 st |                 |                 | 2 nd |                 |                 | 3 rd |         | 4 th  |
|                                                                                                                                           | Control       | 1. Modified BPOC (OHE/OUT/ART/AFT) at the end  |                                                  |                 |                 |                 |                 |                 |                 |                 |                 |         | B
P
O
C |
|                                                                                                                                           |               | 2. Routine oral care at home                   | Continue with standard oral care at home         |                 |                 |                 |                 |                 |                 |                 |                 |         |                  |
|                                                                                                                                           |               | 3. Follow ups                                  |                                                  |                 | 1 st |                 |                 | 2 nd |                 |                 | 3 rd |         | 4 th  |

#### **4.6.1. Intervention groups**

The trial will have one intervention and a control group. The intervention group will receive a modified WHO-BPOC at school and the control will continue with their daily standard of care during the study period.

#### **4.6.2. Intervention period**

The intervention will be instituted immediately after base line data collection and randomization and will be for a period of 24 months follow up.

#### **4.7. Randomization**

Allocation of clusters (secondary schools) into intervention and control groups will be done by stratified block randomization procedure whereby the district will be a stratifying unit and schools a blocking unit. Four randomly selected schools in the three districts will be listed in alphabetical order and assigned numbers 1 to 4. Computer random number generator will be used to randomly allocate 2 clusters in intervention and 2 in control groups in each district. The first two numbers generated will be allocated to intervention and the second two in control.

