## **Budget justification**

A total of TSh 902,900.00 is required to facilitate purchase of stationery and payment for secretarial services. The amount will be used to print, photocopy and bind six copies research proposal. It will also facilitate printing and photocopying of consent forms, questionnaires and clinical data collection forms for 1155 participants. Furthermore, the amount will be used to print and bind 8 thesis reports. A total of TSh 7,320,000.00 is budgeted for payment of allowance for dentists and assistants who will work at the field for a total of 90 days each.

Communication and transport of researchers and assistants to and from field sites during baseline data collection, institution of the intervention and follow ups in 4 districts will require a total of TSh 3,047,600.00. Modified basic package of oral health care will involve treatment and therefore TSh 15,509,000.00 is allocated to facilitate purchase of toothpastes and brushes, dental instruments, dental materials and medical supplies. Data entry and analysis will require a total of TSh 700,000 as payment of data entry clerks and statistician. Local and international conference presentations are required as part of dissemination of findings and fulfilment of PhD and therefore TSh 3,100,000.00 is allocated as travel, accommodation and conference attendance fees.

The proposal will require to be ethically cleared by MUHAS research committee and TDRC in Zambia and for that reason TSh 760,000.00 is allocated for ethical clearance. The study will be done in span of 2 years hence 10% of the budget (TSh 3,121,950.00) is set aside to compensate for inflation and other unforeseen costs. In conclusion a total budget of **TSh 34,341,450.00** is required to facilitate completion of the research project.

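### Section 4.5 selects 18 schools but section 4.7 randomises only 12; on the plan's own inputs 12 schools give about 64–67% power, not 85%

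*Protocol*

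**What the plan says.** Four parts of the protocol describe the number or size of clusters.

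- **Section 4.5 (Sampling).** Three of ten districts are drawn, and "from each district a total of six clusters (secondary schools) will thereafter be selected". To reach 1,760 participants, "18 clusters with cluster size of 90-100 will be involved".
- **Section 4.7 (Randomization).** Districts are strata. Four schools per district are put in alphabetical order and numbered 1 to 4, and "Computer random number generator will be used to randomly allocate 2 clusters in intervention and 2 in control groups in each district". Schools whose numbers come up first and second go to intervention, the other two to control.
- **Section 4.4 (Sample size).** The total of 1,760 is derived for 85% power with an ICC of 0.01. On cluster size: "Estimated cluster size in this study is 80 students in a class".
- **Section 5.0 (Budget and its justification).** The budget pays incentives to 12 teachers, provides "clinical data collection forms for 1155 participants" and covers transport in 4 districts.

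**The concern.** Section 4.7 is the procedure that staff will carry out, and it cannot be applied to six schools per district. Nothing in the protocol says what happens to the other two schools in each district, or how the four that enter the list are chosen from the six.

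In a cluster trial the number of clusters largely determines power. Followed literally, 4.7 drops a third of the schools, and a third of the pupils too if school size stays at 90–100. The protocol would still claim 1,760 participants and 85% power. The budget does not settle which version is meant: 1,155 participants does not agree with 1,760, and 4 districts does not agree with three.

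There is a second, smaller mismatch. The design effect in 4.4 is computed for a class of 80, while 4.5 and 4.7 make the school the cluster.

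**Working it through.** **Inputs, all from section 4.4 unless noted.** The normal point for alpha is "estimated to be 1.96 for 95% Confidence Interval". The point for power "is value corresponding to 85% power of the study =1.03". Sigma is 1.34, which the protocol says "is known mean DMFT from a previous study in Ndola, Zambia"; no standard deviation is given. The difference is 0.268, so the standardised effect is 0.268/1.34 = 0.20. ICC is 0.01 and loss is 10%. School counts and sizes come from 4.5 and 4.7.

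**Step 1: reproduce the plan's figure.**
- 2N = 4 × (1.96 + 1.03)² × 1.34² / 0.268² = 894.01
- Design effect at 80: 1 + 79 × 0.01 = 1.79, and 894 × 1.79 = 1,600.26
- 1,600 × 1.10 = 1,760

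The stated total follows from the stated inputs. At 80 per cluster, 1,760 pupils means 1,760/80 = 22 clusters, not 18.

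**Step 2: power of each design.** Let k be the number of schools, m the enrolled pupils per school, and m′ = 0.9m the number remaining after 10% loss.
- Effective N = k·m′ / [1 + (m′ − 1) × 0.01]
- Power = Φ(0.20 × √(effective N / 4) − 1.96)

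| Design | Pupils after loss | Design effect | Effective N | Power |
|---|---|---|---|---|
| 12 schools × 90 (4.7) | 972 | 1.80 | 540 | 64.2% |
| 12 schools × 100 (4.7) | 1,080 | 1.89 | 571 | 66.7% |
| 12 schools, 1,760 enrolled (147 each) | 1,584 | 2.31 | 686 | 74.5% |
| 18 schools × 90 (4.5) | 1,458 | 1.80 | 810 | 81.2% |
| 18 schools, 1,760 enrolled (97.8 each) | 1,584 | 1.87 | 847 | 82.9% |
| 18 schools × 100 (4.5) | 1,620 | 1.89 | 857 | 83.3% |
| 22 schools × 80 (implied by 4.4) | 1,584 | 1.71 | 926 | 86.1% |

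Worked line for 12 × 90: 0.20 × √(540/4) − 1.96 = 2.324 − 1.96 = 0.364, and Φ(0.364) = 0.642.

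**Step 3: what 4.4's own formula asks for at the planned school size.** With m = 90, 894 × 1.89 × 1.10 = 1,859. With m = 100, 894 × 1.99 × 1.10 = 1,957. That is about 20–21 schools, against 18 schools and 1,760 pupils.

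**Step 4: the budget.** 1,155/12 = 96.25, which would fit 12 schools of 90–100, as would the 12 teacher incentives. The supplies fit neither version. 570 dozen toothpastes over nine rounds is 6,840/9 = 760 recipients, and 380 dozen brushes over six three-monthly rounds is 4,560/6 = 760. An intervention arm would be 880 (half of 1,760) or about 578 (half of 1,155).

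**The case against.** The best case for the plan is that 4.5 and 4.4 agree on 1,760, so 4.7 is leftover wording and the trial will be run with 18 schools. In that case the loss is modest: 81–83% after 10% loss, and 83–85% with no loss. This limits how serious the cluster-size mismatch is. It does not rescue 4.7, which states a complete and different allocation procedure that cannot be run on six schools.

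Four stronger readings are tempting but not supported.

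- A reader might infer that no version of the design delivers 85%. Section 4.4's own version, 1,760 pupils in clusters of 80, gives about 86% after loss. The count of 22 clusters is only implied, but the claim as a general statement is wrong.
- A reader might object that multiplying by 1.10 leaves 1,584 completers, below the 1,600 required. Loss also shrinks each cluster from 80 to 72 and the design effect from 1.79 to 1.71, so 1,584 gives about 86%. The point has no practical weight.
- A reader might take the budget as proof of a deliberate 12-school trial. The protocol never explains 1,155, the supply counts point to 760 recipients, and 4 districts contradicts 4.7 as well. It may be a costing that was not updated.
- A reader might call the 18-school design clearly underpowered because a t reference on schools minus 2 degrees of freedom gives about 76–78% (56–58% for 12 schools). Section 4.4 uses a normal approximation, so this is a sensitivity result, not an error in its arithmetic.

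**Conclusion.** The contradiction between 18 and 12 schools is real and must be resolved before schools are allocated. On the plan's inputs, the scheme in 4.7 falls about 18–21 points short of 85%. Taking more pupils from each of the 12 schools still leaves it about 10 points short. The 18-school design falls about 2–4 points short, which is minor and comes from using 80 in place of the school size.

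These percentages serve mainly to compare the designs. They assume ICC 0.01, equal school sizes, and loss spread evenly so that cluster size falls with it. Holding the design effect at its enrolled size lowers the 18-school, 1,760-pupil figure from 82.9% to 81.0%. If the ICC were 0.02 (an assumption), 18 schools with 1,760 pupils would give about 67%, and 12 schools of 95 about 50%. More basically, 4.4 uses a mean DMFT of 1.34 as the standard deviation, so the standardised effect is 0.20 by construction. Every figure should be recomputed if a true standard deviation is supplied.

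**What to change.** 1. **Section 4.7:** rewrite to match 4.5. List six schools per district, number them 1 to 6, and allocate the first three numbers drawn to intervention and the other three to control. That gives nine schools per arm.
2. **Section 4.4:** use the planned school size in the design effect, keep 1,760 pupils in 18 schools, and restate power as about 83% in place of 85%. State that this rests on 1.34 being used as the standard deviation, and recompute if a true value is found.
3. **If 12 schools are really intended:** correct 18 and 1,760 in 4.4, 4.5 and the Summary (12 schools of 90–100 is 1,080–1,200 pupils) and state power of about 64–67%.
4. **Section 5.0:** bring the participant, teacher, district and supply counts into line with the chosen version.

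The cost of items 1 and 2 is protocol wording and a power figure about two points lower. Keeping 85% is a different choice with a real cost: by 4.4's formula at 90–100 per school it needs 1,859–1,957 pupils in about 20–21 schools. Aligning the budget may change its total, because its participant count is below 1,760.
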